#### Randomisation

Dynamic randomisation will be used to select patients who receive the new program treatment. It is estimated that the population of patients eligible for the program will be higher than the actual amount of patients that can be treated with the program due to restrictions on available personnel, materials and budget. Therefore, randomisation criteria will change dependent on what is logistically possible (= dynamic). Since the reactivation centre has a maximum capacity of 200 patients per year at this time, dynamic randomisation will be carried out by computer where the chance of referral to the program and a stay at the centre will be reduced accordingly as fewer resources are available to provide care and fewer places in the centre are available.

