The program consists of several important elements: First, it aims to identify elderly persons at risk for functional loss at an early stage after hospital admission (= triage within 48 hours of admission). This will make early implementation of interventions possible, which may prevent functional decline and promote a quick return to independent living as well as preserve quality of life [7,22]. Second, the program consists of a combination of integrated interventions offered by a specialized multidisciplinary reactivation team with geriatric expertise. Based on existing literature, this approach is expected to lead to reductions in fall incidence, improved functioning, reduced length of hospital stay, lower (re)admissions to hospital and nursing homes, improved mental well-being of informal caregivers and higher perceived health and life satisfaction among patients as well as better coordination of treatment and follow up between different health care providers and finally, lower mortality [23-34]. Third, the multidisciplinary team uses Goal Attainment Scaling (GAS) to develop and monitor a personalized treatment plan. The GAS method has been successful in maintaining/improving functioning of elderly patients with complex health issues [35,36] and has been standardized for this population [37]. The GAS method consists of several phases: The multidisciplinary team identifies the baseline status of the patient and determines a goal. Then the team will monitor the development per patient and their informal care system by measuring progress regularly, making it possible to adjust interventions and/or goals when necessary. A final GAS measurement will take place to set up a follow up treatment plan before the patient is discharged to the home environment. The fourth element of the program is the possibility for patients with complex problems to be referred by the multidisciplinary team to a stay at a specialized centre for prevention and reactivation (further referred to in this article as "the reactivation centre" or "the centre"). The centre offers a combination of interventions aimed at improving a patient's ability to live as independently as possible in the home environment by providing extra-intensive thematic reactivation treatment alongside regular provisions. It includes specialized nursing home care, paramedical care, specialized mental health care, and treatment and consultations for primary informal caregivers if needed. Patients stay at the reactivation centre for a maximum of three months, after which the multidisciplinary team will develop an individual care-plan for follow up after discharge. Finally, the program will provide support to patients and their informal caregivers by means of a case manager with geriatric expertise who is involved in all aspects of care throughout the period of hospital stay as well as during the follow up period after hospital discharge (irrespective of a patient's destination after discharge whether this is their independent home, the centre for prevention and recovery, a nursing home or any other setting). The case manager is involved in identifying at risk patients in the hospital, coordinating the individual's care plan, coordinating follow up health care for a patient after discharge (e.g. in cooperation with general practitioner, home care or other first line care providers) and aims to support and motivate the patient in treatment adherence. In addition the case manager monitors a patient's risk factors for functional loss throughout all phases of care and may plan extra treatment if necessary as well as improve the care process where possible. Previous programs focused on case management or follow up care have lead to reductions in hospital admissions, nursing home admissions as well as a reduction in length of hospital stay [38,39]. Furthermore, case management may lead to improved access to health care, increased psychosocial support and improved communication with health professionals as valued by patients and their informal caregivers [40].

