#### Blinding

Treatment allocation is by definition un-blinded, but since the hospital based reactivation care program is in fact the usual care provided in the intervention hospital it is possible to maximize blinding of data collectors by describing the three offered health care programs as usual care in all communications, thereby concealing treatment allocation. Furthermore, blinded analyses of data will take place when possible.

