##### Effects and process evaluation of the centre for prevention and recovery

A randomised controlled trial will be analyzed according to the "intention to treat" principle. The process evaluation will study which treatments are carried out in exactly which way. Since differences in case mix and treatment regiments that differ from the program can confound the relation between the program and its expected effects, analysis will be corrected for these possible confounders. For example, data regarding diagnoses of elderly at admission and discharge will be collected and quantitative, clinical treatment data is collected during intake which is focused on medical diagnosis in order to correct for differences in treatment regiments. The randomisation leads to balance between arms of the randomised controlled trial in observed and unobserved predictors of functional decline. Important baseline characteristics are taken into account in analyses to correct for imbalance that might occur by coincidence, thereby increasing power.

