### Strengths

First of all, this study uses a mixed methods design of quantitative and qualitative measures that provide information on three elements as stated by Donabedian [87]: structural issues (e.g. materials, personnel, organization and coordination of care), processes (e.g. activities of professional in diagnosing and treating the patient) and patient and caregiver outcomes such as physical functioning and quality of life. According to Donabedian, the combination of these elements allows for better interpretation of findings, as one method may strengthen interpretation in cases where another method cannot explain variances or outcomes. Qualitative data may generate further hypotheses that may be explained by quantitative process and outcome data. It can also provide a context within which outcomes can be explained more in-depth. Secondly, a pilot study was conducted at the intervention hospital before implementing the program, which optimised beforehand the triage for selecting patients to be included in the main study as well as the power calculations and the practical implementation of the main study. Several practical and implementation problems were encountered in the pilot study (e.g. logistics within hospital, personal communication with hospital personnel etc), making it possible to prevent similar problems and sources of bias when conducting the main study. Within the cohort study, dynamic randomisation will be implemented in order to prevent extra bias and missing data per questionnaire. Furthermore, loss to follow up will be minimized by conducting personal interviews through house calls at three months and 12 months after hospital admission. Finally, the evaluation will be conducting a cost-effectiveness study, which will improve/increase current knowledge on the feasibility of implementing transition programs such as the one evaluated here.

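### The chance of a centre place in the open nested RCT depends on free places that the referring team may know, so assignments can be anticipated and the claimed balance does not follow

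*Protocol article*

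**What the plan says.** Protocol article, Randomisation: "randomisation criteria will change dependent on what is logistically possible (= dynamic"), and "dynamic randomisation will be carried out by computer", under a rule by which "the chance of referral to the program and a stay at the centre will be reduced accordingly as fewer resources are available to provide care"; the chance also falls as places in the centre run out. The reason given is that "the reactivation centre has a maximum capacity of 200 patients per year at this time". The article gives neither the function linking the chance to free places nor its starting value or any lower limit.

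Blinding: "Treatment allocation is by definition un-blinded". The concealment described there is the practice of presenting all three programmes as usual care so that data collectors stay unaware. It does not concern the next assignment.

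Description of the hospital based reactivation care program: one element is "the possibility for patients with complex problems to be referred by the multidisciplinary team to a stay at a specialized centre", with stays of up to three months.

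Population, Inclusion criteria and the triage section: candidates for the centre are defined by thresholds on ISAR-HP, MMSE and NPI, triage data are gathered within 48 hours of admission, and the eligible group is then randomised to 200 with and 200 without a centre stay.

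Effects and process evaluation of the centre for prevention and recovery: "The randomisation leads to balance between arms of the randomised controlled trial in observed and unobserved predictors of functional decline".

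**The concern.** A computer draw hides the random number. It does not hide the probability when that probability is a known function of something people nearby can observe. Here it falls as the centre fills. Someone who knows the occupancy knows whether a place is more or less likely today than last week, and knows the answer outright when the centre is full.

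If those who put patients forward have this knowledge and any latitude over whom they enter or when, patients entered at a high chance can differ systematically from those entered at a low chance. High-chance patients are over-represented in the centre arm, so the difference carries over to the comparison of arms. It may involve motivation or caregiver support, which adjustment for recorded baseline characteristics would not fully capture.

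Separately, a patient assigned when the chance is zero had no possibility of the other arm. Counting that patient in the programme-only arm under intention to treat adds a non-randomised patient to what the Weaknesses section describes as the study's only randomised component.

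**Working it through.** **No plan figure to reproduce.** The power section gives effect sizes and power only for the comparison of hospitals. Those figures reproduce with a two-sided 5% test, which is assumed because none is stated: 95.4%, 83.1% and 95.3% against the stated 95%, 83% and 95%. None concerns the nested trial.

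**Inputs from the article.** 200 centre patients a year, 200 versus 200 in the trial (so at least 400 eligible), and stays of up to three months.

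**Assumptions.**
- Beds: 200 × 91/365 ≈ 50 if every stay is 91 days; 200 × 60.5/365 ≈ 33 if stays are uniform over 30 to 91 days.
- Poisson arrivals over one year, averaging 400, into a centre that starts empty.
- Chance p = share of beds free, or twice that share capped at 0.9.
- Steering: patients entered when p is above its median have a prognosis 0.3 SD better than the rest.

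**Formula.** Arm difference = 0.3 × [Pr(entered at high p | centre) − Pr(entered at high p | no centre)]. The month-stratified figure is the same difference within calendar months, pooled.

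| Beds, stay | Rule | Sent to centre | Arm difference (SD) | Within month (SD) | Assigned at p = 0 |
|---|---|---|---|---|---|
| 50, 91 d | share free | 145 | 0.068 | 0.027 | 0.0% |
| 50, 91 d | twice share | 174 | 0.113 | 0.046 | 0.9% |
| 33, 30–91 d | share free | 141 | 0.061 | 0.036 | 0.0% |
| 33, 30–91 d | twice share | 169 | 0.089 | 0.054 | 0.1% |

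For the first row, 0.068/0.3 ≈ 0.23: the share of patients entered at a high chance is 23 percentage points larger in the centre arm. The range is about 0.06 to 0.11 SD overall. Within months it is about 0.03 to 0.06 SD, the upper end moving between 0.05 and 0.06 with details of the simulation. All these values scale in proportion to the assumed 0.3.

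**How far an assignment can be guessed.** At 400 eligible, an observer who knows p guesses correctly 66 to 70% of the time under these two rules. A constant chance with the same overall share already gives 56 to 65%. Across a wider set of rules and bed numbers the rate runs from about 52 to 75% at 400 eligible and 75 to 85% at 800, where a fixed one-in-four share (200/800) already gives 75%.

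**Constant 1:1 while a place is free.** Among patients actually randomised p is always 0.5, so knowing the occupancy says nothing about the next assignment and the expected steering difference is zero. At 400 eligible, about 9 to 11% arrive when the centre is full and about 176 to 182 reach it in the first year.

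**The case against.** **Staff knowledge is inferred.** No section says that the team sees the number of free places or the current chance, and a computer makes the draw. This stands: the documents support that staff may know, not that they do.

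**Little room to steer.** Eligibility rests on numeric thresholds, triage falls within 48 hours, trained research nurses and students do the interviews, and team referral appears in the programme description rather than in the enrolment steps. The caregiver NPI-Q call decides eligibility only for patients with ISAR-HP below 2 and MMSE above 27. These features narrow the opportunity. They do not close it, and the full protocol, not shown, may lock eligibility before allocation. The capacity-driven chance itself is stated in the article, so it is not a missing detail.

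**Much of the effect is calendar drift.** The simulated centre starts empty, and month stratification removes roughly 40 to 60% of the difference. A residue remains.

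**Stronger readings to avoid.** A reader might infer that the next assignment is largely predictable. That depends on the unstated rule, and setting 66 to 70% against 50% confuses unequal allocation with loss of concealment. A reader might also measure the bias against the 0.2 effect size in the power section, but that belongs to the hospital cohort. Finally, the Strengths section says that "dynamic randomisation will be implemented in order to prevent extra bias and missing data per questionnaire", which might look like a contradiction. The sentence opens by referring to the cohort study, so it is not clearly a claim about the nested trial.

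**Conclusion.** The point holds in limited form. The plan ties the allocation chance to occupancy in an open trial, so the direction of the next assignment can be anticipated by anyone who knows the occupancy, and the result is certain when no place is free. Selective entry is constrained but not excluded, and patients assigned at chance zero are not randomised. The balance claim for the nested trial therefore does not follow from the rule as written.

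The size is not established. The 0.06 to 0.11 SD, and the 0.03 to 0.06 SD left within months, rest on assumed rules, bed numbers and arrivals and on a 0.3 SD steering effect with perfect sorting at the median chance. None of these is in the documents, and there is no effect size for the nested trial to set them against. Assignments at chance zero are under 1% in that scenario but would be more frequent under other rules. The defect is worth correcting because it affects the only randomised comparison and the remedy is simple. It is not evidence that steering will happen.

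**What to change.** 1. Enter consecutive patients who meet the published score criteria, and lock scores, consent and T0 data before the computer looks up capacity.
2. While a place is free, allocate with one constant ratio set in advance.
3. When no place is free, do not randomise. Keep those patients in the cohort as programme without centre, outside the RCT analysis set.
4. Limit the balance claim in the centre evaluation section to patients randomised in this way.

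The work is one reprogrammed rule in the existing allocation computer and a wording change. The price at 1:1 with 400 eligible a year is that about 9 to 11% arrive when the centre is full and leave the RCT set, and that about 176 to 182 rather than 200 reach the centre in the first year. With more eligible patients the excluded share grows, to about a third at 600 and a half at 800, so the ratio should be chosen with the expected number in mind.

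If a varying chance has to stay, the fallback is to record the chance in force at each assignment, analyse conditional on it, and leave out patients assigned at zero.

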### Participants

#### Population

The target population of the study consists of elderly persons (65 years and older) who are at risk for functional loss and are admitted to one of the three hospitals for at least two days. All patients will receive the usual care offered by each of the hospitals. All relevant hospital departments will be included in the study and admission may be elective or acute. Figures 2 and 3 (flowcharts) provide an overview of the flow of patients in the study. Through a first triage step, all patients at risk for functional loss will be identified with the ISAR-HP [46,47]. These at risk patients will be eligible to receive the hospital based reactivation care program and therefore will be asked to participate in the study. In the Vlietland hospital, an additional triage will take place using the short Neuropsychiatric Inventory [48,49] and the Mini Mental State Examination [50] to identify elderly patients eligible for a stay at the reactivation centre. This group will then be randomised to program care including a stay at the centre (n = 200) or program care excluding a stay at the centre (n = 200). The primary informal caregivers of the participating patients will be asked to answer several questions about the patient in a telephone interview as well as fill out mailed paper questionnaires on quality of life, burden of care and other outcomes at time of hospital admission of the patient, three months after hospital admission and twelve months after hospital admission. Furthermore, health care professionals from each participating hospital will be asked to complete a survey on processes of health care.

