#### Power calculation and effect size

For the prospective cohort we expect to be able to collect a sample size of around 1100 patients in the intervention hospital (900 patients treated with the new intervention program and 200 patients treated with the new intervention program including a stay at the reactivation centre). Samples of minimal 500 to 600 patients will be collected in each of the two control hospitals. These estimations are based on the average number of elderly patients who are admitted to the different hospitals during our inclusion period of one year. According to preliminary pilot results on activities of daily living (Katz-15 ADL score), a population of n = 500 in the control hospitals will lead to around n = 300 persons analyzable at three months, whereas a baseline population of n = 1100 in the intervention hospital will lead to around 733 persons analyzable at three months. Using an effect size of 0.25 this will lead to a power of 95% [46]. Furthermore, to detect a smaller effect size (Cohen's D of 0.2), n = 1100 in the intervention hospital and n = 500 for the control hospitals will lead to a power of 83%. If possible, we will aim for a larger sample size in the control hospitals than the expected n = 500, (preferably 900), which will lead to N = 733 analyzable in the intervention hospital versus n = 600 analyzable in the control hospitals, with an effect size of 0.2 leading to a power of 95%. Abovementioned sample sizes are large enough to allow for reliable analysis per subgroup (e.g. subgroup of specific diagnoses) and sets of risk factors.

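### The chance of a centre stay varies with free capacity, so the balance claimed for the randomised comparison holds only among patients with the same allocation probability

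*Protocol article*

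**What the plan says.** The protocol article, under Randomisation, describes a computerised scheme in which "randomisation criteria will change dependent on what is logistically possible (= dynamic". The driver is logistics, not patient characteristics: "the chance of referral to the program and a stay at the centre will be reduced accordingly as fewer resources are available". The stated reason is that "the reactivation centre has a maximum capacity of 200 patients per year at this time".

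Under Population, the same comparison is given with fixed and equal arms: "program care including a stay at the centre (n = 200) or program care excluding a stay at the centre (n = 200". Recruitment takes place "during our inclusion period of one year" (Power calculation and effect size).

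The analysis section on the centre specifies intention to treat and then asserts: "The randomisation leads to balance between arms of the randomised controlled trial in observed and unobserved predictors of functional decline". It adds correction for case mix, diagnoses and differences in treatment regimens, and adjustment for important baseline characteristics to deal with chance imbalance. Date of randomisation, allocation probability and occupancy are not mentioned. The Weaknesses section confirms that the centre evaluation is the only randomised part of the study.

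**The concern.** If the probability of a centre stay is high when places are free and low when they are scarce, the two arms draw on different mixtures of periods. Arm membership is then associated with time and occupancy by design. That association is systematic: a larger sample does not remove it, and it is not the chance imbalance the analysis section has in mind.

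Anything that also moves with time or occupancy can then appear as an effect of the centre, or hide one. Examples are season, case mix, staff workload and the maturity of a newly introduced programme. At stake is the one comparison in the study that is meant to be protected from confounding by randomisation.

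**Working it through.** **The plan's own figures.** No power or effect size is stated for the centre trial. The stated powers concern the hospital comparison. With SD 1 and a two-sided 5% test they reproduce:

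- 733 vs 300 at d = 0.25: 95.4% (stated 95%)
- 733 vs 300 at d = 0.20: 83.1% (stated 83%)
- 733 vs 600 at d = 0.20: 95.3% (stated 95%)

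They do not bear on this point, except to show that a two-sided 5% test is the working convention.

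**Inputs.** From the article: 200 per arm (Population), a one-year inclusion period (Power calculation and effect size), about 60% analysable at three months (Data collection), hence 200 × 0.60 = 120 per arm, and a maximum centre stay of three months (description of the program). Assumed, because the article does not give them: how the allocation probability moves, and how outcomes move over the year.

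**Two-period check.** Let the centre probability be p1 in the first half-year and p2 in the second, with equal numbers in each half and an outcome shift of D (in SD) between halves. With no true effect:

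- absolute bias = D × [p1/(p1+p2) − (1−p1)/(2−p1−p2)]
- type I error = P(|Z + bias/SE| > 1.96), with SE = √(2/120) = 0.129

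| p1 → p2 | D | Bias | Type I error |
|---|---|---|---|
| 0.6 → 0.4 | 0.1 | 0.1 × (0.6−0.4) = 0.02 | 5.3% |
| 0.6 → 0.4 | 0.2 | 0.2 × 0.2 = 0.04 | 6.1% |
| 0.7 → 0.3 | 0.2 | 0.2 × (0.7−0.3) = 0.08 | 9.5% |
| 0.8 → 0.2 | 0.2 | 0.2 × (0.8−0.2) = 0.12 | 15.3% |

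Each row has p1 + p2 = 1, so the expected arms are equal, as the Population section has them. Equal arm totals therefore do not protect against this bias.

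**Simulation.** 400 patients spread evenly over the year, 60% analysable, no true effect, and a linear outcome trend of 0.2, 0.4 or 0.6 SD over the year. Absolute bias and type I error of the pooled comparison:

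| Allocation path | 0.2 SD | 0.4 SD | 0.6 SD |
|---|---|---|---|
| Constant 1:1 | 0.00; 5% | 0.00; 6% | 0.00; 5% |
| Linear 0.6 to 0.4 | 0.01; 6% | 0.02; 6% | 0.04; 6% |
| Linear 0.8 to 0.2 | 0.04; 6% | 0.08; 10% | 0.12; 16% |
| Yearly places used up | 0.05; 7% | 0.10; 14% | 0.16; 23% |
| Beds refilled continuously | 0.02; 5% | 0.02; 5% | 0.04; 6% |

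In the used-up row the chance is 0.1 + 0.9 × (places left/200). In the refilled row there are 200 × 0.25 = 50 beds, each stay lasts three months, and the chance is the share of beds free.

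The linear rows can be checked by hand. If the probability falls by b over the year around a mean of 0.5, bias = trend × (b/12)/0.25 = trend × b/3. For b = 0.6 and a trend of 0.6 SD this is 0.12.

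**After stratifying by month of randomisation.** Bias is within 0.01 SD and type I error between 4% and 6% in every scenario. The simulated standard error of the estimate rises from 0.131 to 0.134 (2%) at the least and from 0.128 to 0.140 (9%) at the most under linear drift. In the used-up scenario it rises from 0.130 to 0.148 (14%) up to 0.128 to 0.152 (19%).

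**The case against.** The strongest reply is that a varying probability does no harm by itself. Bias also needs outcomes or case mix to move with time or occupancy, and the article reports no such trend for the trial population. Its example of changing care, under Weaknesses, concerns a control hospital outside the nested trial. Because a stay lasts at most three months, places turn over; occupancy may rise and fall rather than drift one way, and the bias is then at most about 0.04 SD. Measured case-mix drift would be partly absorbed by the planned adjustment. All of this stands. It limits the size of the problem but does not make the unconditional balance statement correct.

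It can also be said that stratification terms belong in a fuller document. Their absence would be no finding. The finding is that one section fixes a varying probability and another makes a claim incompatible with it.

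Some stronger readings are tempting but not supported:

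- **That the comparison is confounded as a matter of fact.** It is open to confounding; no trend is documented.
- **That early patients fill the centre arm and busy-period patients the other.** Both arms recruit whenever the chance lies between 0 and 1; only the proportions shift.
- **That patients arriving when the centre is full have zero probability and are counted as randomised controls.** The text says the chance is reduced, not that it reaches zero.
- **That staff can foresee allocation and alter whom they put forward.** Triage uses fixed cut-offs and a computer allocates. Nothing says staff see the current probability.
- **That the analysis relies on randomisation alone.** It also adjusts for baseline, diagnosis and treatment differences.
- **That type I error at 200 analysable per arm is the relevant figure.** The article's own 60% gives about 120.

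**Conclusion.** The point holds in this form. The balance statement is wrong for a pooled comparison under the allocation rule the article describes. It is right only conditionally on the allocation probability, and the listed adjustments do not extend to unmeasured factors that follow time or occupancy.

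The possible bias ranges from about 0.02 SD with type I error about 5% (mild drift) to about 0.12-0.16 SD with type I error about 15-23% (strong drift, or yearly places progressively used up). This range rests on assumed allocation paths and trends, no true effect, and about 120 analysable per arm. The lower end would hardly matter; the upper end would. The direction depends on the trend, so a real effect could be masked as easily as a false one produced.

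Separately, the fixed 200 versus 200 is not something a capacity-driven probability guarantees, and the two sections need reconciling.

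**What to change.** 1. Have the randomisation computer store, for each patient, the allocation probability in force and the date of randomisation. If the probability is not kept at the time, it may not be recoverable.
2. Analyse the trial by intention to treat, stratified by allocation probability or calendar block, or weighted by the inverse of the known probability of the arm assigned.
3. Count as trial patients only those randomised with a probability strictly between 0 and 1. Keep any others in the cohort.
4. Reword the balance statement so that it applies conditionally on the allocation probability.
5. Reconcile the fixed arm sizes under Population with the capacity-driven rule under Randomisation.

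The cost is the stored allocation record and a stratified or weighted model. In the simulated scenarios the standard error grows by about 2-9% under linear drift and 14-19% if places are used up progressively. Any patient allocated with certainty leaves the trial set but not the cohort. No extra patients are required.
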